### Interventions

#### Hip strap

The hip strap (*S.E.R.F. strap; DonJoy Orthopedics, Inc., Vista, CA, USA*) will be used with the aim of controlling femoral adduction and internal rotation. The hip strap consists of thin elastic material secured to the proximal portion of the leg that wraps in a spiral fashion around the thigh and is anchored around the pelvis. The line of action of the hip strap pulls the femur into abduction and external rotation [14].

#### Foot orthoses

Foot orthoses will be used with the aim of controlling rearfoot eversion. For such, the participants will use a pair of foot orthoses with semi-rigid arch support and medial elevation of 7° at both the forefoot and rearfoot (Propulsão Produtos Biomecânicos, Minas Gerais, Brazil). The foot orthoses will be made from a block of ethyl vinyl acetate with a thermo-mouldable polymer (shore hardness of 45 A) and will be manufactured by an automated computer numeric control machine (CNC routers) [18].

### Functional tasks

#### Level-ground walking

The participants will perform level walking at a self-selected pace on a 7.3-m walkway. The stance phase during level walking will be determined using an AMTI force plate (model OPT400600HF-2000) embedded in the centre of the walkway and synchronised with the three-dimensional motion analysis system with a sampling rate of 1200 Hz. The walkway will be covered with a rubberised fabric so that the participants will be unaware of the force plate and will consequently not alter their walking pattern. Each participant’s walking speed will be calculated by measuring the average horizontal velocity of the marker mounted on the posterior portion of the pelvis [37]. A trial will be considered valid if the foot of the evaluated lower limb comes into full contact with the force plate during the stance phase of gait [23]. If a trial is not considered valid, an additional trial will be performed. The data from the five trials of level-ground walking at a self-selected pace will be collected for analysis. A 1-min interval between trials will be respected.

#### Single-leg squat test

To perform the single-leg squat test, the participants will stand on the lower limb being evaluated and be instructed to squat more than 60° of knee flexion (downward phase of the manoeuvre—2-s period) and return to the starting position (upward phase of the manoeuvre—2-s period) [12, 38]. A digital metronome will be used to control the single-leg squat rate (15 beats per minute). A repetition will be considered valid when the participant performs the single-leg squat with knee flexion of at least 60° within a period of 4 s without losing balance [12, 38]. If a repetition is not considered valid, an additional repetition will be performed. The data from five trials of the single-leg squat test will be collected for analysis. A 1-min interval between trials will be respected [39].

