**Methods:**

Twenty-nine individuals with PFOA aged 50 years or older will take part in the study. The main outcome is pain intensity. The secondary outcomes are other self-reported measures (global rating of change, acceptable state of symptoms, ease of performance, and confidence) and lower limb kinematics (peak femoral adduction and internal rotation, and peak rearfoot eversion). These outcomes will be assessed during functional tasks performed under three conditions: (i) control condition, (ii) hip strap intervention, and (iii) foot orthoses intervention. To investigate whether these interventions result in the lower limb kinematic changes that they are purported to cause, three-dimensional kinematics of the femur and rearfoot will be captured during each task. Linear mixed models with two fixed factors will be used to test associations between the interventions (control, hip strap, and foot orthoses) and conditions (level-ground walking and single-leg squat test) as well as interactions between the interventions and conditions.

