## Background

Knee osteoarthritis is one of the leading causes of pain and functional disability throughout the world [1]. The most common and symptomatic compartment affected by knee osteoarthritis is the patellofemoral joint [2, 3]. In populations with knee pain or symptomatic knee osteoarthritis, the prevalence of patellofemoral osteoarthritis (PFOA) is 43% [4]. Thus, PFOA constitutes an important source of symptoms and has the potential to exert a negative impact on quality of life due to lifestyle restrictions resulting from pain and functional impairment [5]. The patellofemoral joint is often the first knee compartment affected by osteoarthritis and PFOA is associated with a 5.8-fold greater risk of damage in the tibiofemoral compartment [6]. Thus, PFOA should be considered the focus for the early treatment of knee osteoarthritis [7].

One of the classic symptoms of PFOA is pain in the anterior region of the knee, which is exacerbated by weight-bearing activities that place strain on the patellofemoral joint, such as kneeling and squatting [8]. An altered magnitude or distribution of loading in the patellofemoral joint has been associated with PFOA [8]. Changes in lower limb kinematics, such as excessive femoral adduction and internal rotation during weight-bearing activities, alter the contact between the patella and femoral trochlea, resulting in elevated patellofemoral joint stress [9]. Moreover, excessive subtalar joint pronation (assessed through rearfoot eversion) during the stance phase of gait may result in excessive femur internal rotation and, consequently, result in increased patellofemoral stress [10].

Two studies [11, 12] found also abnormal hip kinematics during functional activities in individuals with PFOA. Crossley et al. [11] found that such individuals walk with greater hip adduction during the late stance phase compared to healthy controls. Carvalho et al. [12] found that individuals with PFOA presented excessive hip adduction at 45° and 60° of knee flexion in both descending and ascending phases of the single-leg squat in comparison to healthy controls. To the best of the authors’ knowledge, only one study [13] investigated foot and ankle characteristics in individuals with PFOA, finding a decrease in ankle dorsiflexion and greater midfoot mobility through clinical measures. These changes may be associated with excessive rearfoot eversion during the stance phase of functional tasks in this population.

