## Methods/design

### Aims

The primary aim of the proposed study is to determine the immediate effects of the hip strap and foot orthoses during level-ground walking and the single-leg squat test on self-reported outcomes. The secondary aim is to investigate whether both the hip strap and foot orthoses result in the kinematic changes that they are purported to cause.

The hypothesis is that the hip strap and foot orthoses will result in immediate improvements in pain intensity and other self-reported measures. We also hypothesise that the interventions will result in a decrease in peak femoral adduction and internal rotation as well as a decrease in peak rearfoot eversion.

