##### Lower limb kinematics

The kinematic variables of interest will be peak femoral adduction and internal rotation and peak rearfoot eversion.

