##### Kinematic data reduction

Kinematic data reduction will be performed with the 3D Motion Monitor software, which will be used for the creation of a biomechanical model of the body segments. Euler angles relative to the static standing trial will be calculated using the joint coordinate system recommendations of the International Society of Biomechanics [45]. Hip joint centre will be determined using the method proposed by Bell et al. [46, 47]. Ankle joint centre will be defined as the midpoint between the medial and lateral malleoli. The kinematic data will be filtered using a 4th-order, zero-lag, low-pass Butterworth filter with a cut-off frequency of 12 Hz.

Femur and rearfoot motion will be calculated relative to the laboratory coordinate system. The kinematic data will be analysed during the stance phase of level walking as well as during the descending and ascending phases of the single-leg squat test. The stance phase of level walking will be defined as the period between initial contact and toe-off. Using a custom MATLAB (MathWorks Inc., Natick, USA) algorithm, initial contact with the force plate will be considered the moment when the vertical ground reaction force (vGRF) first exceeds 10 N and toe-off will be considered the moment when the vGRF falls below a threshold of 5 N [48].

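### Single-leg squat kinematics are peaks with depth open above 60°, so a depth change caused by a device could pass for, or hide, control of femur or rearfoot motion

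*Protocol article*

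**What the plan says.** The Aims section of the protocol article states: "The secondary aim is to investigate whether both the hip strap and foot orthoses result in the kinematic changes that they are purported to cause". According to the abstract, "three-dimensional kinematics of the femur and rearfoot will be captured during each task", so the aim covers walking and the squat. The hypothesis in Aims is worded as a fall in peak angles.

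Under Single-leg squat test, participants will "be instructed to squat more than 60° of knee flexion". A repetition counts when the participant "performs the single-leg squat with knee flexion of at least 60° within a period of 4 s without losing balance". A metronome sets the tempo: 2 s down and 2 s up.

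Under Lower limb kinematics: "The kinematic variables of interest will be peak femoral adduction and internal rotation and peak rearfoot eversion". Kinematic data reduction says that these are analysed in the stance phase of walking "as well as during the descending and ascending phases of the single-leg squat test". No restriction to a common range of knee flexion is stated.

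The Statistical analysis plan section fits linear mixed models with intervention, task and their interaction as fixed effects. It has no term for achieved depth, and it says that the trial will include no additional analyses.

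**The concern.** The floor of 60° makes every valid squat deep enough, but it does not make squats equally deep. A peak over the full movement depends on how far the participant goes as well as on how the limb is controlled at a given depth. The device could plausibly affect depth. The trial hypothesises an immediate fall in pain, which might allow a deeper squat. The strap is elastic and runs from the proximal leg around the thigh to the pelvis, which might restrict the squat. Participants and both assessors know which device is worn.

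The secondary aim asks about mechanism. A smaller peak from a shallower squat would look like motion control without being so, and a deeper squat could hide real control at matched depth. As planned, the squat result could not tell these apart.

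**Working it through.** **What the plan fixes.** The tempo is consistent: 60 s / 15 beats = 4 s per beat, and 2 s + 2 s = 4 s. It fixes time, not depth. A 2-s descent to 60° averages 60/2 = 30° per second and one to 70° averages 70/2 = 35° per second; both satisfy the tempo and the validity rule. Squat depth is therefore bounded below and not above.

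**What could enter the contrast.** For a device against control, write:

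depth-driven difference in peak = (shift in mean depth) × (change in angle per degree of knee flexion beyond 60°).

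The documents give neither input. All values below are assumptions, chosen to show a range that includes no effect.

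| Depth shift | Slope 0 | Slope 0.05 | Slope 0.10 | Slope 0.20 |
|---|---|---|---|---|
| 3° | 0 | 0.15° | 0.30° | 0.60° |
| 5° | 0 | 0.25° | 0.50° | 1.00° |
| 10° | 0 | 0.50° | 1.00° | 2.00° |

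The sign follows the shift. The same product can mask an effect: a true reduction of 1.0° at matched depth, with a squat 10° deeper and a slope of 0.10, gives −1.0 + 10 × 0.10 = 0.

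**How often this would be called significant.** Take one paired comparison in the squat, two-sided 5%, with no true effect at matched depth. This simplifies the planned mixed model. The noncentrality is (difference / SD of paired differences) × √N, with N − 1 degrees of freedom. The plan has 26 participants plus 10% (26 × 1.1 = 28.6, so 29). The SDs of 2° and 4° are also assumed. Probability of rejection at N = 29, with N = 26 in brackets:

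| Depth-driven difference | SD 2° | SD 4° |
|---|---|---|
| 0 | 0.05 (0.05) | 0.05 (0.05) |
| 0.15° | 0.068 (0.066) | 0.054 (0.054) |
| 0.50° | 0.255 (0.232) | 0.100 (0.094) |
| 1.00° | 0.739 (0.688) | 0.255 (0.232) |
| 2.00° | 0.999 (0.998) | 0.739 (0.688) |

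For the 1.00° row with SD 2° and N = 29, the noncentrality is (1/2) × √29 = 2.69. These are not false positives for the total effect on the peak, which really differs in this scenario. They would be false only if read as evidence of control at a given depth.

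**Whether a depth-matched reading is available.** Every valid repetition reaches 60°. Knee flexion must be known for the validity rule, and clusters on the thigh and lower leg are tracked. A reading at 60° can therefore be taken from data already planned.

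**The case against.** The strongest reply is that the peak is a legitimate outcome and matches the hypothesis in Aims. Order is randomised and each participant is their own control, so stable differences in depth between people cancel. A depth change caused by a device lies on the path from device to outcome, and the comparison of peaks remains a valid total effect. This stands. A reader might infer that the secondary aim is confounded. The documents do not support that: depth is a post-randomisation pathway, and the walking kinematics under the same aim do not involve squat depth.

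A reader might also infer that the outcome contradicts the rationale, because Background cites a study in which people with PFOA "presented excessive hip adduction at 45° and 60° of knee flexion in both descending and ascending phases of the single-leg squat". That goes too far. Background also argues from weight-bearing activity in general, from walking and from rearfoot eversion. The cited result concerns hip adduction, whereas this trial measures femur motion relative to the laboratory. The study shows only that a reading at a fixed knee angle is feasible.

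The task is also partly standardised, through tempo, balance, repetition of invalid attempts and familiarisation. That limits variation in depth but does not equalise it across conditions.

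Finally, the exact peak-search window and a description of achieved depth could be left to a fuller document. But the article states the validity rule, the peak outcome and the phases analysed, and excludes additional analyses. As written, nothing separates depth from control.

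**Conclusion.** The point holds for the squat part of the secondary kinematic outcomes, and conditionally. Two things must both be true: a device shifts depth, and the angle keeps changing beyond 60°. The document shows neither, and if either is absent there is no distortion. Under the assumed inputs the depth-driven difference is 0 to 2.0°, and its chance of reaching significance at N = 29 runs from 0.05 to 0.999. So wide a range means that the size is unknown, not that it is large.

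What is weakened is the inference from a change in squat peak to control of the femur or rearfoot. The peak comparison itself, the walking kinematics and the primary pain outcome are unaffected by this point. It is worth correcting because the aim is about mechanism and the remedy is nearly free.

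**What to change.** Keep the peak as the stated outcome and leave the task as it is. For the squat, prespecify:

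1. Peak knee flexion, reported by condition.
2. The same mixed-model comparison between interventions for each kinematic variable at 60° of knee flexion, or for its peak up to 60°, in the descending and ascending phases. These readings exist only for the squat, so the task factor drops out.

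State that a claim that a device controls squat motion will be read with both results beside the peak. Entering achieved depth as a covariate would be a poorer remedy: it adjusts for something that the device may have changed, whereas every valid repetition passes 60°.

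The cost is a change to the data-reduction algorithm and a few sentences in the plan. No further participants or recordings are needed, and the article says that recruitment has not started. The downsides are one extra set of secondary comparisons (3 variables × 2 phases = 6 outcomes) and a stated exception to the exclusion of additional analyses. The added reading says nothing about motion beyond 60°; the retained peak still covers that.

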### Primary and secondary outcome measures and assessment points

The primary outcome will be pain intensity. The secondary outcomes will be other self-reported measures and lower limb kinematic variables, as described below. The data will be collected at a specific time point (Fig. 2). All outcomes will be evaluated by the same assessor.

**Fig. 2 Fig2:**
[figure not shown]
SPIRIT figure of study

#### Primary outcome

##### Pain intensity

Pain intensity will be measured using the visual analogue scale (VAS). This scale ranges from 0 to 100 mm, with the leftward extreme marked zero (absence of pain) and the rightward extreme marked 100 (worst pain imaginable). VAS scores will be computed by measuring the length of the line in millimetres from the extreme leftward mark (no pain) to the mark made by the participant. For the statistical purposes, the average score of the five valid attempts of each functional task will be used [33].

#### Secondary outcomes

##### Global rating of change (GRC) scale

The patient’s perception of improvement or deterioration will be quantified using a GRC scale, which is a 15-point Likert-type scale that measures the patient’s impression of a change in health status following a specific treatment [40]. The scale ranges from − 7 (great deal worse) to + 7 (great deal better), with 0 indicating no change. Changes of 4 points or more on this scale have been previously considered clinically important in patients with knee pain [41, 42]. This scale will be applied for both conditions (hip strap and foot orthoses).

##### Acceptable state of symptoms

The acceptable state of symptoms will be assessed by asking the participants the following question: “Considering your usual level of pain and your functional disability to perform daily tasks, if you performed this functional task (level-ground walking or single-leg squat test) with the approach used in this intervention (hip strap or foot orthoses) from now on, would you consider your current state to be satisfactory?” [43]. The participants will answer “yes” or “no”. The question will be posed for both conditions (hip strap and foot orthoses).

##### Ease of performance

To assess the ease of performance during each task, the participants will use a 5-point Likert scale to rate how easy each test was to perform: (i) markedly hard, (ii) somewhat hard, (iii) neither hard nor easy, (iv) somewhat easy, or (v) markedly easy [22].

##### Knee confidence

Knee confidence will be measured using a 100-mm VAS with the following question: “How confident did you feel completing that task?” (terminal descriptors: 0 mm = very confident; 100 mm = not confident at all) [24].

##### Lower limb kinematics

The kinematic variables of interest will be peak femoral adduction and internal rotation and peak rearfoot eversion.

##### Kinematic analysis

Kinematic analysis will be performed using a three-dimensional motion analysis system (Vicon Motion Systems Ltd., Oxford, UK) with six cameras (sampling rate of 120 Hz) during the level-ground walking and single-leg squat tests. Data will be acquired using the Nexus Systems 2.1.1. software (Vicon Motion Systems Ltd., Oxford, UK) and 3D Motion Monitor Software (Innovative Sports Training, Chicago, IL, USA).

After the system is calibrated, reflective markers (14 mm in diameter) will be positioned on the following anatomic landmarks: greater trochanter, medial and lateral femoral condyles, medial and lateral malleoli, and base of the fifth metatarsal (on the shoe). Two tracking markers (clusters) consisting of four non-collinear markers will be fixed to a rigid base and attached to the posterolateral portion of the thigh and lower leg using velcro straps. Another cluster consisting of three non-collinear markers fixed to a rigid base will be attached to the rearfoot directly on the calcaneus using double-sided adhesive tape. For this step, the shoes will be customised; an opening in the posterior region will be made to enable the cluster to be attached directly to the calcaneus (Fig. 3). Previous studies have shown that the placement of calcaneal markers on shoes may overestimate the movements of the rearfoot [44]. A static standing trial will be performed to align the subject with global coordinates and provide a reference for further analysis.

**Fig. 3 Fig3:**
[figure not shown]
Customised neutral shoes (Nike® model *Flex Experience RN 2 MSL*) with opening in posterior region to allow cluster to be attached directly to calcaneus for kinematic analysis

##### Kinematic data reduction

Kinematic data reduction will be performed with the 3D Motion Monitor software, which will be used for the creation of a biomechanical model of the body segments. Euler angles relative to the static standing trial will be calculated using the joint coordinate system recommendations of the International Society of Biomechanics [45]. Hip joint centre will be determined using the method proposed by Bell et al. [46, 47]. Ankle joint centre will be defined as the midpoint between the medial and lateral malleoli. The kinematic data will be filtered using a 4th-order, zero-lag, low-pass Butterworth filter with a cut-off frequency of 12 Hz.

Femur and rearfoot motion will be calculated relative to the laboratory coordinate system. The kinematic data will be analysed during the stance phase of level walking as well as during the descending and ascending phases of the single-leg squat test. The stance phase of level walking will be defined as the period between initial contact and toe-off. Using a custom MATLAB (MathWorks Inc., Natick, USA) algorithm, initial contact with the force plate will be considered the moment when the vertical ground reaction force (vGRF) first exceeds 10 N and toe-off will be considered the moment when the vGRF falls below a threshold of 5 N [48].

### Data management

The data will be stored in the UFSCar Physical Therapy Department on a secure computer server with password-protected file, to which only the researchers will have access. Files with the participants’ information will be coded with individual identification codes. The first author will have a backup copy of all data.

### Data monitoring

The researchers involved in the study will be responsible for the monitoring of the protocol, along with any relevant changes that may occur during the development of the study. The Postgraduate Program of the university will supervise the integrity of the data, and the Internal Data Monitoring Committee will have access to the condition to which each participant was assigned, while the whole analysis will be confidential.

### Harms

Adverse events will be collected after the individuals have provided consent and enrolled in the study. Harm and complications from the interventions, if any, will be reported when reporting the results of this trial. Harm will be categorised as serious and minor adverse events.

### Provisions for post-trial care

The first author will be responsible for any injury that occurs during the assessment session and will sign a document for each participant attesting to her commitment to provide any medical treatment, if necessary, in coordination with the Physical Therapy Department at UFSCar.

